**4. Other precautions while taking this medication:**

1) Follow the prescribed dosage and administration instructions carefully.

2) Be cautious of overlapping ingredients when taking with other herbal (medicinal) preparations.

3) When giving this medication to children, ensure it is taken under the guidance and supervision of a guardian.

4) Do not insert a spoon that has been soaked in hot or cold water into the medication bottle (for extract preparations).

5) When reusing a medication spoon, clean it thoroughly without any moisture before using it again (for extract preparations).

**5. Storage precautions**

1) Store in a cool, dry place away from direct sunlight (ensure it is tightly sealed after use).

2) Keep out of reach of children.

3) Do not transfer the medication to another container, as this may lead to misuse or deterioration in quality. Always keep it in its original container and ensure it is tightly closed.

**1 3. Criteria for discontinuation and withdrawal of subjects, and termination of the clinical trial**

The participation status of all subjects in this clinical trial will be recorded. If the administration of the investigational medicinal product or observation is discontinued, the reason will be documented. The conditions under which a subject may discontinue participation are as follows:

- ① In case of acute reactions (allergy, hypersensitivity, etc.) to the herbal preparation.
- ② If it is found that a subject does not meet the inclusion/exclusion criteria.

- ③ If unforeseen diseases or accidents occur making administration and observation impossible.
- ④ If "serious adverse reactions" or "severe adverse drug reactions" occur, making continued administration and observation inappropriate.
- ⑤ If the subject becomes pregnant.
- ⑥ If the subject or their proxy requests to discontinue participation (withdrawal of consent).
- ⑦ Any other reasons deemed appropriate by the researcher for discontinuing the trial.

The termination criteria for this clinical trial are as follows.

The clinical trial will be terminated when the target number of subjects is enrolled, and data integrity is ensured. The principal investigator will record the termination date and conduct data analysis once the follow-up for the last subject is completed. For individual subjects, the clinical trial will conclude upon completion of planned visits and evaluations, and the processes specified in the protocol.

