## 14. Statistical Analysis Methods

### 14.1 General principles of result analysis

The primary analysis for efficacy evaluation will use the Full Analysis Set (FAS). Safety evaluations will be conducted using the Safety Set. All statistical tests will be two-sided with a significance level of 5%. For efficacy evaluation, missing data in the FAS will be handled using the Last Observation Carried Forward (LOCF) method for statistical analysis, while all other data will be analyzed as originally recorded.

**Safety Set (SS):** A group of subjects who have received the investigational medicinal product at least once and have undergone at least one safety-related follow-up.

**Full Analysis Set (FAS):** A group of subjects who, in accordance with the ITT principle, have received the investigational medicinal product and have at least one measurement of the primary efficacy variable.

For analyses other than efficacy evaluation, such as feasibility evaluation (e.g., recruitment rate, dropout rate, reasons for dropout), the recruitment rate will be calculated as the number of enrolled subjects divided by the total number of screened subjects (%). Dropout rates and

reasons will be analyzed descriptively for both the entire study and each herbal preparation group.

To compare differences between groups for efficacy variables, ANCOVA will be conducted with the assigned group as the factor and the baseline value as the covariate (two-sided  $p < 0.05$ ). If assumptions of ANCOVA (normality, homoscedasticity) are violated or outliers are observed, Ranked ANCOVA will be performed. For categorical data, frequencies and percentages will be calculated, and comparisons between groups will be made using the Chi-square test or Fisher's exact test (if expected frequency is  $\leq 5$ ). Statistical analyses will be conducted using R-software (latest version) or jamovi software (latest version).

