#### **15. Criteria, methods, and interpretation of efficacy evaluation**

##### **15.1 Evaluation items and methods**

###### **15.1.1 Primary evaluation variable**

- 1) FSS score after 12 weeks of intervention

FSS scores will be compared between groups after taking 12 weeks of intervention.

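### Section 13 does not separate stopping the product from leaving the study, so some obtainable Week 12 FSS values can be replaced by carried-forward ones

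*Protocol*

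**What the plan says.** Section 13 opens by mentioning both kinds of discontinuation together: "If the administration of the investigational medicinal product or observation is discontinued, the reason will be documented". It then gives a single list, introduced by "The conditions under which a subject may discontinue participation are as follows". The seven conditions are, in order:

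1. acute reaction to the preparation;
2. ineligibility, worded as "If it is found that a subject does not meet the inclusion/exclusion criteria";
3. an unexpected illness or accident that rules out both dosing and follow-up;
4. serious or severe reactions that make continued administration and observation inappropriate;
5. pregnancy;
6. withdrawal of consent;
7. "Any other reasons deemed appropriate by the researcher for discontinuing the trial".

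The primary variable is the FSS at the end of treatment. Section 15.1.1 says: "FSS scores will be compared between groups after taking 12 weeks of intervention". Section 14.1 defines the full analysis set (FAS) as dosed subjects with at least one FSS measurement, describes it as following ITT, and states: "missing data in the FAS will be handled using the Last Observation Carried Forward (LOCF) method for statistical analysis".

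Three other places bear on what happens after discontinuation:

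- Section 11.4.1.7 names early dropout as a reason for an unscheduled visit, at which the Visit 4 tests are done so far as feasible. The Schedule Summary marks the FSS for that visit.
- Sections 16.4, 19 and 20.7 describe follow-up after an adverse event, for safety purposes only.
- Section 22 ends compensation for visits after the point of discontinuation.

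**The concern.** Stopping a product and ceasing to be observed are different events. A subject who has a rash, becomes pregnant or is found ineligible after randomisation can often still fill in a nine-item questionnaire at Week 12. If the plan gives such a subject no status other than having left, that score is not requested and an earlier one is analysed in its place.

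Which data are collected is fixed by the protocol. No analysis plan can recover a Week 12 score that was never requested. Fatigue may also change between the last score and Week 12, so the carried value can misstate the outcome. If the loss differs between arms, the primary comparison shifts. Section 7 says that the results will be used to size a confirmatory trial, so a distortion here could be passed on.

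**Working it through.** **Is the gap there?** Setting the sections side by side:

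- Section 13 concerns participation. It has no category for subjects who are off the product but still followed.
- The visit descriptions (11.4.1.3, 11.4.1.4) and the Schedule Summary do not say that these visits continue after the product is stopped.
- Section 11.4.1.7 gives an FSS dated at dropout, not at Week 12.
- Section 22 pays for no later visit, which fits none being planned.

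**Which conditions does it reach?** Week 12 FSS is in principle obtainable under conditions 1, 2, 5 and 7, and under condition 4 where observation remains appropriate. It is not obtainable under condition 3 as worded, nor under condition 6.

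**Can these situations arise after dosing?** Yes. Section 11.4.1.1 asks for documentary confirmation of COVID-19 only where possible, and Section 11.4.2.1 rechecks participation in other trials at each visit. Ineligibility can therefore surface late. Section 12 lists skin and digestive reactions, and lack of improvement, among reasons to discontinue the medication, so stopping can be related to tolerability or outcome.

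**Size.** The protocol states no dropout rate, effect size or SD, so there is no figure of its own to reproduce. What follows is illustration.

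*Assumptions:* FSS changes linearly over 12 weeks; the last FSS is at week t; a fraction d of an arm is lost avoidably; the missing Week 12 value would have stayed on the arm's line. For an arm with mean change c, the expected LOCF mean change is (1 − d)·c + d·c·t/12. Differences are active minus placebo, and higher FSS is worse.

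*No true effect, both arms fall by 1.0, t = 4:*
- Error per carried value = 1.0 × (1 − 4/12) = 0.67.
- Loss of 20% active and 10% placebo (10 and 5 of 50): 0.67 × (0.20 − 0.10) = +0.067.
- The reverse split: −0.067.
- 10% against 5%: 0.67 × 0.05 = 0.033.
- 20% against 10% with t = 8: 1.0 × (1 − 8/12) × 0.10 = 0.033.
- 20% against 10% with the screening value carried (t = 0): 1.0 × 0.10 = 0.10.

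*Assumed true difference −0.50 (placebo −1.0, active −1.5), t = 4:*

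| Loss, active / placebo | LOCF difference |
|---|---|
| 5% / 5% | −0.483 |
| 10% / 10% | −0.467 |
| 20% / 20% | −0.433 |
| 20% / 10% | −0.367 |
| 10% / 20% | −0.533 |

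For the fourth row: active 0.8 × (−1.5) + 0.2 × (−0.5) = −1.300; placebo 0.9 × (−1.0) + 0.1 × (−0.333) = −0.933; difference −0.367.

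*Scale:* with 50 per arm and an assumed FSS SD of 1.0 to 1.5, the standard error of the difference is SD × √(2/50) = 0.20 to 0.30. A bias of 0.067 is 22% to 33% of that.

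**The case against.** The strongest case on the other side is that Section 13 is permissive. It says when a subject may leave and forbids no later assessment. It also names stopping the product and stopping observation as two events in its opening. A reader might infer that Section 13 requires participation to end; the wording does not support that. What stands is narrower: continued assessment is nowhere provided for, so handling is left to each of the two sites.

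Four further limits hold.

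- A reader might infer that only consent withdrawal should entail loss of follow-up. The list contradicts this: condition 3 applies where observation is impossible, and condition 4 where continuing administration and observation is inappropriate.
- A reader might assume that the screening FSS is what gets carried. The early-dropout visit makes a later value available in many cases. Carrying the screening value requires both Visit 2 and the dropout FSS to be missed. The FAS definition does allow this, because it does not ask for a post-baseline score.
- Ineligibility is fixed before randomisation and is found under double blinding, so there is no reason to expect it to differ by arm. By itself it would dilute a true effect slightly; it would not create a false one. Arm-dependent loss is plausible mainly for reactions.
- The ITT contrast should not be pressed. Dosed subjects found ineligible remain in the FAS. The weakness is that an earlier score stands in for their Week 12 score.

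This is also a pilot with no power claim, and dropout is itself a feasibility outcome. That lowers the stakes but does not make the lost scores recoverable.

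**Conclusion.** The point holds as a gap in data collection. The protocol does not separate stopping the product from leaving the study, and it makes no provision for Week 12 FSS from subjects who stop but could and would give it. LOCF then fills the gap.

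The bias is probably small and its direction is unknown: about 0.07 points under the illustrative 20% against 10% split, and 0.03 to 0.10 across the other unequal splits shown under no true effect. Each figure treats all the assumed loss as avoidable. Real dropout also includes withdrawn consent, loss to follow-up and impossible observation, which no change to Section 13 would recover, so total dropout should not be read as the amount at stake. An effect on the SD used for later planning is possible but has not been quantified. The change is worth making because it is cheap and the loss cannot be repaired afterwards.

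**What to change.** Leave all stopping criteria as they are. When the product should be stopped is a clinical matter and is not in question here.

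- Split Section 13 into *stopping the investigational product* and *withdrawal from the study*. Limit the second to consent withdrawn, lost to follow-up, or observation impossible or judged inappropriate.
- State that subjects who stop the product, including those found ineligible after randomisation and dosing, are asked with their consent to complete the FSS at the remaining scheduled visits through Week 12.
- State in Section 14.1 that these scores are used in the FAS in place of carried-forward ones.
- Keep the self-completed format of Section 11.4.2.13 where possible, since telephone collection would change the mode for exactly these subjects.
- Align Section 11.4.1.7, so that a dropout visit does not replace the Week 12 assessment, and Section 22, so that attended follow-up visits are compensated.

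Cost: an amendment to the wording, a few extra nine-item questionnaires, and visit payments. At the present rates in Section 22, a subject who stops before Visit 2 and attends Visits 2 to 4 would receive 50,000 + 50,000 + 100,000 = 200,000 KRW, which is already part of the planned 350,000 KRW per participant.

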## 14. Statistical Analysis Methods

### 14.1 General principles of result analysis

The primary analysis for efficacy evaluation will use the Full Analysis Set (FAS). Safety evaluations will be conducted using the Safety Set. All statistical tests will be two-sided with a significance level of 5%. For efficacy evaluation, missing data in the FAS will be handled using the Last Observation Carried Forward (LOCF) method for statistical analysis, while all other data will be analyzed as originally recorded.

**Safety Set (SS):** A group of subjects who have received the investigational medicinal product at least once and have undergone at least one safety-related follow-up.

**Full Analysis Set (FAS):** A group of subjects who, in accordance with the ITT principle, have received the investigational medicinal product and have at least one measurement of the primary efficacy variable.

For analyses other than efficacy evaluation, such as feasibility evaluation (e.g., recruitment rate, dropout rate, reasons for dropout), the recruitment rate will be calculated as the number of enrolled subjects divided by the total number of screened subjects (%). Dropout rates and

reasons will be analyzed descriptively for both the entire study and each herbal preparation group.

To compare differences between groups for efficacy variables, ANCOVA will be conducted with the assigned group as the factor and the baseline value as the covariate (two-sided  $p < 0.05$ ). If assumptions of ANCOVA (normality, homoscedasticity) are violated or outliers are observed, Ranked ANCOVA will be performed. For categorical data, frequencies and percentages will be calculated, and comparisons between groups will be made using the Chi-square test or Fisher's exact test (if expected frequency is  $\leq 5$ ). Statistical analyses will be conducted using R-software (latest version) or jamovi software (latest version).

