|                                                    | ●Take, ○Do not take                                                                                                                                                                                                                                                                                                                                                                                                                                                                                                                                                                                                                                                                                                                                                                                                                           |       |                                     |
| Efficacy Evaluation Variables               | 
Primary endpoint
 
1) Change in FSS score after 12 weeks of intervention.
 
Secondary endpoint
 
1) Final medication adherence.
 
2) Differences in final medication adherence between groups.
 
3) FSS scores at visits 2 and 3.
 
4) ChFS total and subscale scores at visits 2, 3, and 4.
 
5) EQ-5D-5L scores at visit 4.
 
6) PSQI-K Global score at visit 4.
 
7) K-MOCA total and domain scores at visit 4.
 
8) BDI scores at visit 4.
 
9) DF, DB, and DF-DB scores at visit 4.
 
10) Computerized neurocognitive function test scores at visit 4.
 
11) SPPB test scores for walking speed, standing test, static balance test, and total score at visit 4.
 
12) Analysis of recruitment rates, dropout rates, and reasons for dropout.
 |       |                                     |

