| Statistical Analysis Method | 
General Principles of Outcome Analysis
 
Data for efficacy evaluation will primarily use the Full Analysis Set (FAS). Data for safety evaluation will be assessed from the Safety Set (SS). All statistical tests, unless otherwise specified, will be two-tailed with a 5% significance level. For efficacy evaluation, in cases where there are missing values in the FAS, the Last Observation Carried Forward (LOCF) method will be applied for statistical analysis, and all other analyses will be conducted with the original data.
 
Full Analysis Set (FAS): Following the ITT principle, this set includes participants who have received the herbal medication and have at least one measurement of the primary efficacy variable.
 
Safety Set (SS): This set includes participants who have received the intervention at least once and have undergone safety-related follow-up at least once.
 
Analysis of Primary Endpoint
 
1) FSS Scores After 12 Weeks of Intervention
: FSS scores are compared between groups after taking 12 weeks of intervention.
 
Analysis of Secondary Endpoints
 
1) Final Medication Adherence
: Present the mean, standard deviation, median, minimum, and maximum values of the final medication adherence rate (%) for all participants at 12 weeks (Visit 4 or termination point).
 
2) Difference in Final Medication Adherence Between Groups
: Present and compare the mean, standard deviation, median, minimum, and maximum values of the final medication adherence rate (%) for both groups at 12 weeks (Visit 4 or termination point).
 |

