## Schedule Summary

| Visit                                                                      | 0       | One  | 2      | 3      | 4       | UV * |
|----------------------------------------------------------------------------|---------|------|--------|--------|---------|------|
| Week (day)                                                                 | -1 (-7) | 1(0) | 4 (28) | 8 (56) | 12 (84) | -    |
| Visit window (day)                                                         | -       | +2   | ±2     | ±2     | ±2      | -    |
| Written Consent                                                            | ●       |      |        |        |         |      |
| Demographic Survey                                                         | ●       |      |        |        |         |      |
| Participation in Other Clinical Trials                                     | ●       |      |        |        |         |      |
| Physical Exam                                                              | ●       |      |        |        |         |      |
| Medical History                                                            | ●       | ●    |        |        |         |      |
| COVID-19 Diagnosis                                                         | ●       |      |        |        |         |      |
| Concomitant Medication/Treatment                                           | ●       |      |        |        |         |      |
| Vital Signs                                                                | ●       | ●    | ●      | ●      | ●       | ●    |
| Electrocardiogram                                                          | ●       |      |        |        | ●       | ●    |
| Laboratory Test                                                            | ●       |      |        |        | ●       | ●    |
| Immune, Metabolite Test (Blood Collection)                                 | ●       |      |        |        | ●       | ●    |
| Pregnancy Status Evaluation **                                             | ●       |      |        |        |         |      |
| Fatigue Symptom Evaluation ***                                             | ●       |      |        |        |         |      |
| FSS (Fatigue Severity Scale)                                               | ●       |      | ●      | ●      | ●       | ●    |

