#### **14.3 Analysis of efficacy variables**

##### **14.3.1 Primary efficacy variable**

FSS score after 12 weeks of intervention

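### LOCF is the only missing-data rule for the primary FSS analysis, and the FAS wording leaves open whether a screening score can stand in for week 12 or only completers count

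*Protocol*

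**What the plan says.** Protocol section 14.1 makes the FAS the primary set for efficacy and states that "missing data in the FAS will be handled using the Last Observation Carried Forward (LOCF) method for statistical analysis". The Statistical Analysis Method row of the Summary says the same: "the Last Observation Carried Forward (LOCF) method will be applied for statistical analysis". No other way of handling missing efficacy data is named.

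The FAS is said to follow the ITT principle and consists of participants who "have received the investigational medicinal product and have at least one measurement of the primary efficacy variable". The primary variable is "FSS score after 12 weeks of intervention" in section 14.3.1 (section 15.1.1 agrees) and "Change in FSS score after 12 weeks of intervention" in the Summary. The model in section 14.1 is ANCOVA with group as factor and the baseline value as covariate, tested two-sided at 5%.

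The Schedule Summary places FSS at Visit 0 (screening), at Visits 2, 3 and 4 (weeks 4, 8 and 12) and at unscheduled visits. It is not scheduled at Visit 1. Section 11.4.1.7 lists early dropout among the reasons for an unscheduled visit and asks for the Visit 4 tests there where feasible, but does not require them. Section 7 sets the sample at 50 per arm and says the results will be used to size later confirmatory trials.

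**The concern.** The FAS sentence can be read in two ways, and neither works well with LOCF.

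- **Any FSS counts.** FSS is an eligibility test, so every treated participant already has one. Someone lost before week 4 without an exit FSS then has the same number as ANCOVA covariate and as week-12 outcome, a change of exactly zero. Someone lost later keeps a week-4 or week-8 score. These values enter the model as if observed at week 12.
- **Only the week-12 FSS counts.** The FAS becomes week-12 completers, which conflicts with its stated ITT principle, and LOCF has nothing to fill for the primary endpoint.

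On the first reading, carried scores leave out the change that would have followed dropout. If FSS falls over 12 weeks in both arms, a difference in dropout becomes a difference between treatments. If the drug works, even equal dropout shrinks its estimated effect. Some fall in both arms is plausible, because entry requires a screening FSS of at least 4 and the score can then regress toward the mean. The estimate goes on to inform the size of the next trial.

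**Working it through.** The protocol gives no effect size, SD, dropout rate or expected FSS fall, so it has no figure to reproduce. From the documents: 50 per arm, two-sided 5%, ANCOVA with baseline covariate, FSS at weeks 0, 4, 8 and 12.

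**Assumed:** SD 1.2; between-visit correlation 0.6; linear change; dropout unrelated to outcome and spread evenly after Visits 0, 2 and 3; placebo fall 1.0 point; drug-arm fall 1.0 (no effect) or 1.6 (benefit 0.60).

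**Step 1, change lost per dropout.** The carried score omits 1, 2/3 or 1/3 of the 12-week change, on average 2/3. With dropout d, an arm with true fall F shows F × (1 − 2d/3).

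**Step 2, true benefit 0.60.**

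| Dropout drug / placebo | Drug fall | Placebo fall | Estimated benefit |
|---|---|---|---|
| 15% / 15% | 1.6 × 0.900 = 1.44 | 1.0 × 0.900 = 0.90 | 0.54 |
| 25% / 5% | 1.6 × 0.833 = 1.33 | 1.0 × 0.967 = 0.97 | 0.37 |
| 5% / 25% | 1.6 × 0.967 = 1.55 | 1.0 × 0.833 = 0.83 | 0.71 |

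Simulation gave the same values to within 0.01. ANCOVA on observed week-12 scores gave 0.60 in all three.

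**Step 3, no drug effect.** Bias = dropout gap × 2/3 × fall. SE ≈ 1.2 × √(1 − 0.6²) × √(2/50) = 0.96 × 0.2 = 0.192.

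- Gap 0, fall 1.0: bias 0; simulated error rate 4.9%.
- Gap 10 points, fall 1.0: bias 0.067, or 0.35 SE; approximation 6.4%, simulated 5.6–6.5%.
- Gap 20 points (5% vs 25%), fall 1.0: bias 0.133, or 0.69 SE; approximation 10.7%, simulated 10.1–10.6%.
- Gap 20 points, fall 0.5: bias 0.067; approximation 6.4%, simulated 6.2–6.7%.

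**Step 4, range under other assumptions** (no drug effect, SD 1.0, correlation 0.5, 8,000 simulated trials each; error rate for a fall of 1.0 / 1.5):

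| Dropout | Spread evenly | All carry screening score |
|---|---|---|
| 20% vs 10% | 6.6% / 8.4% | 8.1% / 11.6% |
| 25% vs 10% | 8.5% / 12.1% | 14.1% / 19.8% |
| 30% vs 10% | 11.5% / 18.0% | 19.6% / 32.4% |

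At 25% vs 10% and a fall of 1.0, varying SD over 0.8–1.3 and correlation over 0.3–0.7 gives 6.8–10.4% (even spread) or 9.0–17.6% (all carry the screening score). Without LOCF, observed-case ANCOVA stayed near 5% throughout.

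**Step 5, would a clearer FAS be enough?** Requiring a post-baseline FSS but keeping LOCF gives 7.2% (fall 1.0) and 9.7% (fall 1.5) at 25% vs 10%. The distortion shrinks but does not disappear.

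**Step 6, sizing the next trial.** At fixed SD the required number varies as 1/effect². Relative to 0.60, planning on 0.54 multiplies it by (0.60/0.54)² = 1.23, on 0.37 by 2.63, and on 0.71 by 0.71.

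**The case against.** A reader might infer that LOCF here doubles the false-positive rate. The documents do not support that as a property of the plan. Inflation needs unequal dropout together with a fall in FSS in both arms, and the protocol gives a figure for neither. With equal dropout and no drug effect the test holds its level.

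Nor is it settled that every treated participant enters on a screening score. Sections 14.3.1 and 15.1.1 define the primary variable as the week-12 score, and a screening score is not that. The unscheduled-visit provision also limits baseline carry-forward. If nobody carries the screening score, the 5% vs 25% case with a 1-point fall gives 8.2% instead of about 10%.

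A third inference, that the bias flatters the drug, is also unsupported. It does so only if placebo loses more participants; if the drug arm loses more, the bias runs against the drug.

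The trial is also a pilot. Dropout is to be reported by group with reasons, so an imbalance would be visible, and the 0.06 shrinkage at equal dropout is about a third of the standard error (0.06/0.192 = 0.31).

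These points limit the size and the grade. They do not remove the defect. The FAS sentence still has two incompatible readings, and an exit score taken early is still carried to week 12. The protocol itself fixes LOCF, so this is not a detail left to a statistical analysis plan. One caution applies to the calculations: they compare LOCF with observed-case ANCOVA under dropout unrelated to outcome, where the latter is unbiased by construction. The mixed model proposed below was not simulated.

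**Conclusion.** The concern holds in conditional form. LOCF is a weak primary method here, and the FAS wording must be settled. If any FSS qualifies, a true 0.60-point benefit becomes 0.54 at 15% dropout in both arms, and 0.37 or 0.71 at 5%/25% splits. With no drug effect the error rate is near 5% with equal dropout, about 6% with a 10-point gap, and about 10–11% with a 20-point gap and a 1-point fall in both arms. These figures rest on SD 1.2, correlation 0.6, linear change and dropout spread evenly over visits and unrelated to outcome, none of which the protocol gives. Other plausible inputs move the error rate both ways, as the ranges show. If only the week-12 FSS qualifies, none of these figures applies, and the fault is instead a completers-only set labelled ITT.

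The main consequence is for the effect estimate passed to the confirmatory trial. Any effect on the SD was not quantified. This should be fixed, but it does not invalidate the pilot.

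**What to change.** In section 14.1 and the Summary:

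1. Replace LOCF as the primary method with a mixed model for repeated measures on FSS at Visits 2, 3 and 4, with treatment, visit, treatment-by-visit, baseline FSS, baseline-by-visit and site, and an unstructured covariance. Take the Visit 4 treatment contrast as primary. The model uses the observed week-4 and week-8 scores without treating them as week-12 values, and it remains valid if dropout depends on scores already observed.
2. State that the FAS needs at least one post-baseline FSS. Alternatively, keep all treated participants by modelling Visit 0 as a response with a mean common to both arms.
3. Keep LOCF only as a sensitivity analysis.

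The cost is protocol wording (and the analysis plan's, if there is one), some programming, and possibly a slightly wider confidence interval. No new data or visits are needed.
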